## Abstract

**Background:**

Humanoid robots are being used more frequently in health care: in geriatrics and pediatrics, robots such as “Pepper” and “Nao” have been shown to enhance communication, emotional well-being, and patient engagement. During the pandemic, their role expanded, for example, to include remote monitoring and reducing the risk of infection. Given these applications, our study examines the integration of 2 advanced humanoid robots, Pepper and Nao, within the reception area of a geriatric hospital.

**Objective:**

The study aims to develop a reception service directed to enhance the quality of the IRCCS Istituto Nazionale di Riposo e Cura per Anziani (INRCA), Ancona, Italy. The primary end point of the study is the assessment of the perceived quality of an innovative reception service. Second, the study aims at evaluating the usability, human-robot interaction, user experience, and technical performance of the solution.

**Methods:**

The HOSPER (analysis of the quality of reception services using robotic platforms, Nao and Pepper) study is a feasibility pilot project coordinated by IRCCS INRCA. During the trial, 200 older adults using services at IRCCS INRCA in Ancona will be enrolled. Two humanoid robots, Nao and Pepper, which are already available at the hospital, will be used to support reception and orientation services. Data collection will include general demographics, cognitive and functional status, usability measures, perceived service quality, and human-robot interaction indicators.

**Results:**

The recruitment and data collection started in January 2025 and will be concluded by December 2025. Results regarding the feasibility of a robotic-based reception service in a geriatric hospital will be published in 2027.

**Conclusions:**

The HOSPER study aims to assess the feasibility of an innovative robot-mediated reception service in a geriatric hospital, with specific focus on recruitment feasibility, completion rates, user acceptability, and perceived service quality. In fact, the usability and user experience evaluation will demonstrate the feasibility of the approach and provide indications for future developments and improvements.

## Introduction

### Background

Hospital reception and orientation represent critical first touchpoints in the patient experience [1-3]. In geriatric settings, the process of navigating an unfamiliar hospital environment to reach the correct department or exam location is often associated with anxiety, confusion, and poor first impressions of care [4,5]. These challenges are particularly acute for older adults, who may experience navigation difficulties due to cognitive or sensory changes, physical fatigue, or limited familiarity with institutional settings [6,7]. Current human-staffed reception services, while important, are often resource-constrained and may not fully address the emotional and relational dimensions of a welcoming care experience [3,8]. In recent years, social and socially assistive robots (SAR)—autonomous machines with humanoid features designed to interact empathetically with humans—have demonstrated promise both in health care settings and in interactions with older people [9,10]. Systematic reviews confirm the effectiveness of SAR in maintaining cognitive and physical functions, promoting sociability and emotional support, and reducing feelings of loneliness and anxiety among older adults [11,12]. These robots have been successfully deployed across diverse health care contexts, from therapeutic interventions with children and individuals with autism to supportive roles in geriatric care facilities [13-15]. Prior work highlights that SAR can engage older adults in meaningful interactions, improve mood and cooperation during care activities, and enhance perceived quality of care experiences [16,17]. A growing body of evidence suggests that robots possess specific affordances for the reception and orientation context: they can provide consistent, patient, and nonjudgmental guidance; they can communicate in multiple languages and adapt their communication style to individual needs; and their embodied, interactive presence may reduce anxiety and foster a sense of welcome that improves the initial hospital experience [18-20]. On this basis, we hypothesize that deploying SAR as reception agents can improve older adults’ perceived quality of the reception and orientation experience, as well as the usability and acceptability of the service. However, current research on social robots and SAR in health care focuses on therapeutic, rehabilitative, or patient care activities. The application of SAR specifically to hospital reception and orientation services—particularly in the Italian health care context—remains understudied. Thus, a feasibility pilot is warranted to assess whether this innovation can be successfully integrated into routine hospital operations and whether it meaningfully enhances older adults’ experiences during intake.

### Goal of the Study

The HOSPER (analysis of the quality of reception services using robotic platforms, Nao and Pepper) study aims to assess the feasibility of assigning receptionist duties in an Italian geriatric hospital to two widely used SAR in research and health care settings, Nao and Pepper (both developed by SoftBank Robotics). These robots were selected because they offer multimodal interaction capabilities (voice, gesture, and visual interface), are highly customizable, and are already available at the IRCCS INRCA (Istituto Nazionale di Riposo e Cura per Anziani) hospital. Thus, this protocol focuses on improving the perceived quality of the reception and orientation experience for older adults, rather than directly measuring navigation performance (eg, time or errors). Therefore, the primary outcome is perceived service quality, with secondary outcomes capturing usability, human-robot interaction (HRI) quality, and emotional responses during robot-mediated guidance.

## Methods

### Study Design

The HOSPER study is a feasibility pilot study coordinated by IRCCS INRCA. Its aim is to assess the perceived quality of an innovative reception service through the introduction of 2 robotic platforms designated to provide information on how to reach the location where the person will receive the service of interest.

During the trial period, 200 older adults referred to IRCCS INRCA in Ancona will be enrolled. Figure 1 shows the study design, which consists of 2 different phases: recruitment (T0) and interaction (T1).

**Figure 1. F1:**
[figure not shown]
The study design. SPMSQ: Short Portable Mental Status Questionnaire; SUS: system usability scale.

A total of 200 older adults will be recruited for this single-center feasibility pilot with a pragmatic quasi-experimental design. For logistical reasons, entire days will be dedicated to either Nao or Pepper. Participants will be equally allocated to interact with Nao or Pepper based on alternating study days and a predetermined quota system: once 100 participants have interacted with one robot, all subsequent participants will use the other robot until a total of 100 participants are reached for each. The allocation schedule will be predetermined and documented to ensure transparency.

### Participants

The inclusion and exclusion criteria are reported in Textbox 1.

Textbox 1.Inclusion and exclusion criteria for patients.
**Inclusion criteria**
Aged 65 years and olderCapacity to consentPossession of full cognitive abilities (Short Portable Mental Status Questionnaire=0)
**Exclusion criteria**
Failure to meet the inclusion criteriaConcomitant participation in other interventional studies based on human-robot interactionLack of written informed consentPacemaker wearerSignificant visual or hearing impairment

### Equipment

For this study, 2 humanoid social robots already available at IRCCS INRCA will be used: NAO v6 (58 cm in height) and Pepper (120 cm in height), both developed by SoftBank Robotics. The HOSPER applications for both platforms were developed using the Choregraphe software (Nao v2.8.6.23 and Pepper: v2.5.10.7; SoftBank Robotics), with standardized interaction flows programmed via “choice” objects handling up to 30 ward inputs. Interactions follow identical scripted sequences: they are user-initiated by the keyword pronunciation (HOSPER), followed by a fixed welcome prompt, speech recognition (ie, desired ward to reach), path directions provided by the robot (during this passage Pepper also shows a visual map on the tablet), repetition on request (≤40% understanding), and standardized closure. Detailed technical development is reported in Amabili et al [21]. Figure 2 shows the dedicated area and one of the robots. This is a closed box in which the robots will be located. Figure 2A shows the experimental setting, while Figure 2B focuses on the experimental setting with the high-definition camera that will record HRI.

**Figure 2. F2:**
[figure not shown]
The experimental setting. (A) Dedicated area for the study with 1 robot (Pepper). (B) Focus on the experimental setting with a high-definition camera to record the human-robot interaction.

### Outcomes

#### Overview

The primary end point of the study is the assessment of the perceived quality of an innovative reception service, as measured by the Customer Satisfaction Questionnaire.

The secondary end points are (1) assessment of the usability of 2 robotic platforms by older adults for hospital reception, as measured by the system usability scale (SUS) [22]; (2) analysis of HRI using the Godspeed Questionnaire [23]; (3) dynamic analysis of the interaction and user experience using the Noldus system [24]; and (4) analysis of robot logs to assess technical performance.

As this is a feasibility study, these outcomes will be interpreted descriptively. For the primary end point, we will examine mean scores on the Customer Satisfaction Questionnaire and the proportion of participants reporting medium-to-high satisfaction levels to judge whether the robot-mediated reception service is acceptable to older adults. For the secondary end points, the distributions of SUS, Godspeed Questionnaire scores, and Noldus-derived emotional indicators will be used to evaluate whether usability, HRI quality, and emotional responses are compatible with moving towards a larger-scale trial. In addition to these measures, the study will use standard feasibility indicators, including recruitment rate, the proportion of participants who complete the interaction and postinteraction assessments, and completeness of data collected at T0 and T1. These indicators will be summarized descriptively to judge whether the protocol is feasible in routine practice. Finally, qualitative notes on technical performance (eg, malfunctions, interruptions, or need for operator intervention) will be collected throughout the study both during the sessions and through the analysis of video recordings to inform the system-level feasibility of the robot-mediated reception service and guide future updates of the service.

While outcomes focused on usability and HRI emphasize validated patient-reported measures, triangulation is provided through existing data sources: Noldus video analysis for objective emotional and behavioral indicators, and robot logs capturing interaction duration, comprehension rates, and repetition requests as objective efficiency metrics. In fact, these complementary data sources mitigate self-report limitations while remaining within the approved protocol scope.

Finally, as this is a feasibility pilot, a priori success criteria are defined. The study will be considered feasible if: (1) at least 70% of eligible older adults approached agree to participate; (2) at least 70% of enrolled participants complete the interaction with the assigned robot and the postinteraction assessment; and (3) questionnaire data are complete for at least 80% of enrolled participants. These thresholds are intended to inform the design and sample size of a subsequent definitive trial rather than to support hypothesis testing.

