### Procedure

#### Recruitment (T0)

The robots will be placed in a dedicated area (a closed box) at the hospital entrance. Only one user will be allowed in at a time. A researcher will stop users at the hospital entrance and invite them to participate in the study. Participants must confirm their willingness to participate in writing. After signing the consent forms, the technology will be assigned to them in a randomized alternating manner (ABAB) according to the order of inclusion of participants. Then, the researcher will collect general information about the patient and administer the cognitive scale to verify that the user meets the inclusion criteria.

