#### Interaction With the Robot (T1)

The user, who has been deemed suitable and agreed to participate, starts the interaction with the robot assigned. In both cases, the researcher will suggest touching the robot’s head to initiate the interaction. From this point onwards, the researcher will not intervene in the interaction between the user and the robot, and the user will be free to interact with the robot and to stop the interaction at any time. When an explicit support request is made by the user, the researcher can intervene a maximum of 3 times, in line with good practice in experiments involving HRI analysis. At this point, the robot greets the user and asks how they can be helped, using the phrase “Good morning and welcome to INRCA. I’m (robot’s name) and I’m here to provide useful information to help you reach your desired destination within the hospital. Which department do you need to reach, or which exam do you need to take? Please, answer by saying only the name of the department or the exam as soon as my eyes turn blue.” At this point, the user responds, and the robot replies in one of two ways:

If it does not understand the request (or if the request is outside the robot’s knowledge), it invites the user to rephrase it and they return to the previous point; andIf it understands the request, it explains the path that the user should follow. In the case of Pepper, this path will also be shown on a display with photographic materials integrated with directional arrows.

After 1 successful interaction or 2 failed attempts, the robot asks the user if it has provided all the necessary information. If so, the robot says goodbye to the user as follows: “Thank you for participating. Have a nice day.” Otherwise, the interaction resumes from the point where the robot asks for the department to be reached or the test to be performed.

The researcher suggests that the user should touch the robot’s head to stop the session only in the case of an interaction loop or if the user is willing to stop the interaction.

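### Success criterion 1 is a rate among eligible people approached, but eligibility is tested only after consent and robot assignment, so it is unknown for those who decline and the criterion cannot be evaluated as written

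*Protocol article*

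**What the plan says.** The Overview under Outcomes in the protocol article sets three success criteria:

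- Criterion 1 concerns recruitment: "at least 70% of eligible older adults approached agree to participate".
- Criterion 2 concerns completion of the session: "at least 70% of enrolled participants complete the interaction with the assigned robot and the postinteraction assessment".
- Criterion 3 concerns data completeness: "questionnaire data are complete for at least 80% of enrolled participants".

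Recruitment (T0) gives the order of events. It starts with the approach: "A researcher will stop users at the hospital entrance and invite them to participate in the study". Assignment follows consent: "After signing the consent forms, the technology will be assigned to them in a randomized alternating manner (ABAB) according to the order of inclusion". Eligibility comes last: "Then, the researcher will collect general information about the patient and administer the cognitive scale to verify that the user meets the inclusion criteria". The T1 section then admits only confirmed users: "The user, who has been deemed suitable and agreed to participate, starts the interaction with the robot assigned".

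Textbox 1 makes an SPMSQ result an inclusion criterion. The Statistical Analysis section adds that feasibility indicators will use denominators restricted to complete cases.

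**The concern.** A proportion of eligible people approached needs the number of eligible people among those who agreed and among those who refused. The first is observed. The second is not, because the SPMSQ is given only to people who have already consented, and the article describes no eligibility check before the invitation. The Discussion says that older adults with cognitive impairment are a substantial part of the population using this hospital, so ineligibility on this test is unlikely to be negligible.

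Criterion 1 is one of three conditions for declaring the study feasible, and the article says that the thresholds will inform the design and sample size of a later trial. If its value cannot be computed, the team will have to choose a substitute denominator after the data are in, and different substitutes give different answers.

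A smaller, related problem affects criteria 2 and 3. They are stated per enrolled participant, while the Statistical Analysis section points to complete cases for the same indicators.

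**Working it through.** **Plan's own figures.** The 70%, 70% and 80% thresholds are set as targets and are not derived, and 200 is simply 100 + 100. There is nothing further to reproduce.

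**What is observed for criterion 1**

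| Group | SPMSQ taken? | Eligibility known? |
|---|---|---|
| Approached, consented | yes, after assignment | yes |
| Approached, declined | no | no |

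**Formula.** Let *c* be the share of those approached who consent, *ec* the eligible share among consenters (observed), and *ed* the eligible share among decliners (not observed). Then

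criterion 1 = *c*·*ec* / [*c*·*ec* + (1 − *c*)·*ed*].

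The documents give none of the three, so every value below is an assumption.

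**Worked case, per 1,000 approached, *c* = 60%, *ec* = 80%.** 600 consent, of whom 480 are eligible; 400 decline.
- *ed* = 50%: 200 eligible decliners; 480/(480 + 200) = 70.6%, criterion met.
- *ed* = 80%: 320 eligible decliners; 480/(480 + 320) = 60.0%, criterion not met.

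**Range**

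| *c* | *ec* | *ed* = 30% | *ed* = 50% | *ed* = 80% | *ed* = 100% |
|---|---|---|---|---|---|
| 60% | 60% | 75.0% | 64.3% | 52.9% | 47.4% |
| 60% | 80% | 80.0% | 70.6% | 60.0% | 54.5% |
| 65% | 80% | 83.2% | 74.8% | 65.0% | 59.8% |
| 70% | 80% | 86.2% | 78.9% | 70.0% | 65.1% |
| 75% | 60% | 85.7% | 78.3% | 69.2% | 64.3% |
| 75% | 80% | 88.9% | 82.8% | 75.0% | 70.6% |

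**Break-even.** Setting the formula to 0.70 gives *ed*/*ec* = [*c*/(1 − *c*)] × (0.3/0.7). This is 0.64 at *c* = 60%, 0.80 at 65%, 1.00 at 70% and 1.29 at 75%. Below the break-even ratio the criterion is met; above it, it is not. At 75% consent, decliners would have to be more often eligible than consenters for the criterion to fail. With *ec* = 80% it is met even if every decliner was eligible (0.60/0.85 = 70.6%).

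**Two substitutes disagree.** Consenters over all approached equals *c*, which matches criterion 1 only if *ed* = *ec*. Eligible consenters over all approached equals *c*·*ec*. At *c* = 70% and *ec* = 80% these are 70% and 0.70 × 0.80 = 56%.

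**Denominator of criteria 2 and 3, passages side by side**
- The success criteria use enrolled participants, a term the article does not define.
- Study Design says 200 will be enrolled and fills the quota with 100 people per robot who have interacted. Read literally, someone who is eligible but never starts would drop out of the denominator, and the interaction half of criterion 2 would be close to automatic.
- Statistical Analysis restricts the denominators of feasibility indicators to complete cases. Read literally, criterion 3 becomes complete questionnaires divided by complete questionnaires, which is 100% by construction, and criterion 2 is pushed the same way.

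**The case against.** The strongest reply is that giving a formal cognitive test only after written consent is ordinary practice, and that criterion 1 can be read as apparently eligible at approach. Age, a pacemaker, evident sensory impairment or participation in another robot study can be asked at the door. Much of this stands: only the decliners' SPMSQ component is unobservable in principle, and the remedy for criterion 1 is largely a restatement along those lines. But the article does not say that anything is asked at approach, and the criterion says eligible without qualification.

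A second reply is that the thresholds are descriptive and that neither the primary end point nor the Nao–Pepper comparison uses criterion 1. That is true and limits the consequences. The article nevertheless uses these criteria to declare the study feasible.

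A third is that a journal article may leave the definition of enrolled to the full protocol. By itself that would be fair. What remains is that the article's own success criteria and its complete-case rule give different denominators for the same indicators.

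Two stronger readings are tempting. A reader might infer that people who fail the SPMSQ count as enrolled non-completers, so that completion can never exceed the SPMSQ pass rate. The documents do not support this: the 200 to be enrolled are the same 200 who fill the interaction quota, and only users found suitable start. A reader might also infer that screen failures use up places in the ABAB sequence. That is not established either: the alternation follows the order of inclusion, and the quota counts people who have interacted.

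**Conclusion.** The point holds for criterion 1. With the stated order of procedures, its denominator includes a group whose eligibility is never determined, so the criterion cannot be evaluated as written.

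The size depends on rates that the documents do not give. Under moderate assumptions (60% consent, 80% of consenters eligible) the result is 70.6% or 60.0% according to whether 50% or 80% of decliners were eligible. At high consent with a high pass rate the problem fades: at 75% and 80% the criterion is met whatever the decliners' status. Very wide ranges, such as 47% to 100%, need a low assumed pass rate and the extreme case that all or none of the decliners were eligible, and should not be taken as forecasts.

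For criteria 2 and 3 the conclusion is narrower. The denominator needs one definition, because the article points to more than one; it does not follow that either criterion is bound to fail.

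**What to change.** - **Criterion 1.** Restate it as: *at least 70% of persons aged 65 or older approached, without an exclusion evident at approach, give consent*. Report the SPMSQ pass rate among consenters separately. This needs a short tally at the entrance of people approached, their age group and any evident exclusion. Data Management says screening data are deleted at project completion, so the counts must be tabulated before then.
- **Criteria 2 and 3.** State that *enrolled* means consented and confirmed eligible, whether or not the interaction was started or completed. Screen failures are then excluded and non-completers stay in. Amend the complete-case rule in Statistical Analysis so that it does not override this for the feasibility indicators.
- **Assignment.** For remaining participants, assign the robot after the SPMSQ, so that eligibility is decided before allocation. Where a whole day is given to one robot, as Study Design describes, the robot is known beforehand and the re-ordering changes little; the conflict between that rule and ABAB is a separate matter.

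**Cost.** Wording, a tally sheet, and two steps of one visit in a different order. Criterion 1 becomes consent among apparently eligible people, which is not quite the quantity first intended. Recruitment began in January 2025, so the re-ordering cannot apply to people already recruited, and for those already approached the restated criterion can be computed only if suitable counts were kept.
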